## Assessments

An overview of variables is shown in table 4.

**Table 4 T4:** Variable overview

	Study visit	1	2	3	4	5	6	7	8	9	10	Comment
	Week	-5t_1/2_	0	1	2	3	4	5	6	26	**30-52 **^1)^	^1) ^in euthymic phase
	Test											
	Informed consent	X										
Diagnostic interview	SCID or MINI plus	X										
	Inclusion/exclusion criteria	X										
NORBRAIN Entry Questionnaire NEQ	Socio demography Medical history etc	X										
	PANSS	X										
	GAF	X							X	X	X	
	Clinical examination	X										
	Current and concomitant medication	X	X	X	X	X	X	X	X	X	X	
Health related Quality of Life	SF 36	X							X	X	X	
Efficacy	MADRS	X	X^2)^	X	X	X	X	X	X^2)^	X	X	^2) ^audio taped
	IDS	X	X^2)^	X	X	X	X	X	X^2)^	X	X	^2) ^audio taped
	CGI-BP	X	X	X	X	X	X	X	X	X	X	
	PGI-I			X	X	X	X	X	X	X	X	
	YMRS	X	X	X	X	X	X	X	X	X	X	
	MSIF	X								X	X	
Relapse	Interview									X	X	
Overall cognitive function	MMS ^3)^		X	X	X	X	X	X	X			^3) ^in ECT-group only
Neuropsychological assessment		X							X	X	X	
	EMQ	X							X	X	X	
Adverse events	Interview UKU		X^4)^			X			X			^4) ^previous med.
	SAE-form			X	X	X	X	X	X			
Lab	Cytokines	X							X	X	X	
	Cortisol ^5)^								X			^5) ^morning cortisol in blood
	Other, incl cortisol^6)^	X										^6) ^as specified in Blood samples
	ECG ^7)^	X										^7) ^if indicated
	EEG	X										
	MRI caput	X										
Substance abuse	Urin	X										
Pregnancy	Urin ^8)^	X										^8) ^fertile woman
Compliance	Interview			X	X	X	X	X	X	X	X	
Compliance	Blood sample					X						
Temperament	TEMPS-A									X		
Migrene	Interview	X								X		

### Initial Subject and Disease Characteristics

Diagnosis is made on the basis of clinical interview and verified by the MINI-International Neuropsychiatric Interview (MINI) [36] plus or The Structured Clinical Interview for DSM-IV Axis I Disorders (SCID-I) [37]. All the patients are described by a modified version of Stanley Foundation Bipolar Network Entry Questionnaire (NEQ) at baseline [38,39].The first part of the questionnaire elicits data regarding vocational, educational, and economic status, onset and course of illness, family history, and past treatment. The second part assesses cycling and seasonal patterns, medical problems, medications (past and present), ability to function and symptomatic status, precipitants of illness (e.g. substance use), treatment adherence, and insight into the illness [38]. History of ECT is also assessed. At baseline symptom intensity will be measured by MADRS [40], Inventory of Depressive Symptoms (IDS) [41], Clinical Global Impression bipolar (CGI-BP) [42], and YMRS [43]. Global Functioning will be assessed with Global assessment of functioning (GAF) [44]. Health-related quality of life will be assessed with SF-36 [45]. There will be performed a medical examination, MRI Caput, ECG (if indicated), EEG, and laboratory tests. Substance abuse will be assessed by interview and urine test. Fertile woman are tested for pregnancy.

### Efficacy

#### Primary response variable

Patients will be interviewed at start (visit 2), weekly on week 1-5 (visit 3-7), on week 6/endpoint (visit 8), on a follow-up-visit after 26 weeks (visit 9) and in case of depressive, manic or mixed symptoms at weeks 26 on a control-visit between 26-52 weeks (visit 10). Visit 10 should be performed in euthymic state if possible. Patients will be interviewed using MADRS. The primary response variable is change in total MADRS-score at endpoint versus baseline.

#### Secondary response variables

IDS [41], CGI-BP [42]), GAF [44], Patient Global Impression of Improvement (PGI-I),

YMRS [43], SF-36 [45], Multidimensional Scale of Independent Functioning- MSIF [46], proportion in each group attaining remission, time to remission, proportion in each group attaining response, time to response, relapse (new episode).

##### Definitions

Response: at least a 50% reduction of the baseline MADRS score.

Remission: MADRS score of 12 or less at the end of trial.

New episode: A patient who has previously responded to treatment meets the DSM-IV criteria for Major Depressive Episode or Manic episode.

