Current use of all other psychotropic medication during the study period with the exception of the following: The use of alimemazine (max dose 30 mg daily), chlorpromazine (max dose 25 mg × 2 daily) and chlorprothixene (max dose 20 mg × 2) is allowed. The use of mianserine (max dose 10 mg daily) is allowed. Medication related to the ECT procedure is allowed.
For Medication in control group refer to Medication in control group - Treatment As Usual
Inability to comply with study protocol
Unstable serious medical conditions, including clinically relevant laboratory abnormalities
Conditions that affect neuropsychological assessment such as Parkinson's Disease, Multiple sclerosis, stroke, alcohol and substance abuse or dependence (according to SCID or DSM-IV-TR)
Fertile women without adequate contraception (Adequate contraception includes: abstinence, oral contraceptives, intrauterine devices, barrier method)
Young Mania Rating Scale (YMRS) [43] of 20 or more
Patient at high suicidal risk according to clinicians' judgement

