#### Withdrawal criteria

The patient will be withdrawn from the study if the clinician finds that the patient is in need of, or better served with other treatment, or if Exclusion criteria are met. The patient will also be withdrawn from the study if the clinical condition gets significantly worse according to the clinicians' judgement or if patients withdraw their consent. The date and the reason for discontinuation are noted. All patients prematurely discontinuing the trial must be seen for a final evaluation.

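### Response and remission rest on MADRS alone, so a patient whose MADRS falls during a manic switch can count as a success, even if withdrawn for reaching the trial's YMRS limit

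*Protocol article*

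**What the plan says.** The Definitions section of the protocol article gives "Response: at least a 50% reduction of the baseline MADRS score" and "Remission: MADRS score of 12 or less at the end of trial". Neither refers to manic symptoms. Statistical analysis compares both rates by chi-square and analyses time to each by survival methods.

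Mania appears elsewhere in four ways:
- YMRS is marked at all ten visits in Table 4 ("YMRS X X X X X X X X X X").
- Secondary response variables lists YMRS as an outcome of its own, not linked to response or remission: "YMRS [43], SF-36 [45], Multidimensional Scale of Independent Functioning- MSIF [46], proportion in each group attaining remission, time to remission".
- Table 2 excludes patients with "Young Mania Rating Scale (YMRS) [43] of 20 or more", and Withdrawal criteria removes a patient who is "better served with other treatment, or if Exclusion criteria are met".
- A manic episode can be a relapse: "New episode: A patient who has previously responded to treatment meets the DSM-IV criteria for Major Depressive Episode or Manic episode".

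Patients who leave early are analysed by last observation carried forward (LOCF). A completers' analysis is additional.

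**The concern.** Every participant has bipolar disorder, and the two arms receive very different treatments: ECT against a drug algorithm that includes antidepressants. Equal rates of switching into mania cannot be taken for granted. A switch can bring the MADRS down without the patient being well. The plan treats marked mania as grounds for exclusion and withdrawal, yet its two binary success definitions do not look at mania.

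At stake is the reading of four secondary results: the response rate, the remission rate, time to response and time to remission. If one arm has more switches, these outcomes would credit it for them. Reporting YMRS separately would show the switches but would not change who was counted as a success.

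**Working it through.** **1. The plan's own figure.** Inputs from Sample size calculation: difference 4, SD 7, two-sided alpha 0.05, power 0.90. Equal allocation is assumed, as the article states no ratio.
- Normal approximation: n per arm = 2 × (1.960 + 1.282)² × 7² / 4² = 64.4, rounded up to 65, or 130 in total.
- Exact t-test: 65.33, rounded up to 66 per arm, or 132 in total, with power 0.903.

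The stated 132 reproduces. It rests on mean MADRS change, so no change to the response or remission definitions alters it.

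**2. One hypothetical patient traced through the rules.** Take baseline MADRS 25 (the entry minimum) and, at a treatment-phase visit, MADRS 8 with YMRS 25.
- Response: (25 − 8)/25 = 68%, at least 50%, so met.
- Remission cut-off: 8 is not above 12, so met.
- Withdrawal: YMRS 25 is at or above 20, so an exclusion criterion is met.
- After withdrawal, the last MADRS is carried forward. If it is the 8, the patient is a responder and a remitter at endpoint. Withdrawal criteria also requires a final evaluation; if MADRS is rated there, the carried value may itself be taken during mania.

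No stated rule scores this patient as a non-responder.

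**3. The opposite case.** With the same baseline and YMRS but MADRS 20 (a mixed picture), the reduction is (25 − 20)/25 = 20%, so there is no response. A switcher can count as a success but need not.

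**4. Do other parts of the plan correct the classification?**
- The new-episode outcome presupposes an earlier response and does not revoke it. Table 4 places the relapse interview only at visits 9 and 10, after the six-week endpoint at visit 8.
- The completers' analysis drops withdrawn switchers instead of counting them as failures, and it is only additional.
- A YMRS rise that stays below 20 does not meet that exclusion criterion at all.

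**5. Size.** One patient in 66 is 1/66 = 1.5 percentage points. The documents give no switch rate, so the table is illustrative. It assumes a true non-manic response of 40% in both arms, 66 per arm, and an added share of patients in each arm who meet the MADRS rule only while manic. The last column is the approximate chance that the chi-square test is significant in favour of the first arm.

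| Added share, first vs other arm | Patients of 66 | Apparent difference | Chance |
|---|---|---|---|
| 5% vs 5% | 3.3 vs 3.3 | 0 points | 2.5% (nominal) |
| 5% vs 2% | 3.3 vs 1.3 | 3 points | 5% |
| 10% vs 5% | 6.6 vs 3.3 | 5 points | 8% |
| 10% vs 2% | 6.6 vs 1.3 | 8 points | 15% |
| 15% vs 5% | 9.9 vs 3.3 | 10 points | 21% |
| 15% vs 2% | 9.9 vs 1.3 | 13 points | 32% |

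If the shares are read as switch rates, every switcher is taken to meet the MADRS cut-off and to do so only because of the switch. The differences are then upper bounds for those rates.

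**The case against.** The strongest reply is that the definitions ask a narrower question, whether the depression improved, and that mania is followed separately. YMRS is a secondary outcome, CGI-BP rates mania as well as depression at every visit, manic relapse has its own definition, and treatment-emergent adverse events are analysed. Keeping the two poles apart is a legitimate choice. This stands as a reason to retain the MADRS-only rates. It does not show how many of the successes were manic at the time.

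A reader might infer more than the text supports:
- *That the definitions contradict the withdrawal rule.* They do not. One describes a symptom outcome and the other the patient's disposition. The gap is that no rule links them.
- *That every switcher counts as a success.* Step 3 of the working shows otherwise.
- *That a patient can be a responder and a new episode at the same visit.* The definition describes a sequence, and the relapse interview comes only after the endpoint.
- *That the bias is 3 to 8 points.* Those figures come from assumed switch rates of 5–10% against 2%.

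A further objection concerns the remedy. In Table 4 only MADRS and IDS at visits 2 and 8 are audio-taped for co-rating by staff outside the patient's treatment. YMRS is not taped, and Methodological weaknesses says the assessors are not blinded. Making YMRS part of the only definition would bring an unmasked rating into endpoint response and remission. That stands, and it favours an added analysis over a replacement. It weighs less for time to response and time to remission, because the MADRS ratings at weeks 1 to 5 are not taped either.

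**Conclusion.** The point holds in a limited form. Response and remission are blind to mania, and LOCF can keep a patient withdrawn for reaching the YMRS limit among the successes. Whether this biases the comparison depends on unequal switch rates, which the documents neither give nor rule out. With equal rates both arms' figures may be inflated, with little or no bias in the difference. The only size that can be stated without a switch rate is 1.5 points per reclassified patient, at an assumed 66 per arm. Only secondary outcomes are affected; the definition of the primary outcome and N = 132 stand. This is a cheap improvement, not a flaw in the main comparison.

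**What to change.** Keep the MADRS-only rates. Beside them, prespecify an analysis of response, remission, time to response and time to remission in which:
- a patient counts as a success at a visit only if YMRS at that same visit is below the trial's existing limit of 20, the investigators to confirm that limit for this purpose;
- a patient withdrawn for reaching that limit counts as a non-responder and non-remitter, in place of the LOCF value.

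Do not add a manic or mixed episode diagnosis at each visit. Table 4 schedules the diagnostic interview only at visit 1 and the relapse interview only at visits 9 and 10, so the weekly data for it would not exist.

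The cost is wording and one extra set of tables, with no new data and no change in sample size. There are three downsides. The rates will be slightly lower. The YMRS condition depends on unmasked ratings that are not audio-taped. Hypomania below the limit, relevant because bipolar II patients are eligible, is still not captured.

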### Assessment of trait-like characteristics

The Temperament Evaluation of Memphis, Pisa, Paris and San Diego-auto questionnaire (TEMPS-A) [47] will be assessed at follow up and migraine diagnostic [48] pre-treatment and at follow up (week 26).

### Safety assessment

Safety data will include:

Clinical examination; electrocardiogram (if indicated); blood tests as described below (supplemented by others if clinically indicated) at start; urine test for substance abuse: amphetamine, cannabis, opiates, benzodiazepines, cocaine, methadone, pcp, zopiclone, buprenorphine, carisoprolol.

MMS weekly first six weeks in ECT-group to assess global cognitive functioning.

### Blood samples

A routine battery of blood measures will be analyzed at the local hospital biochemistry units:

Leucocytes, haemoglobin, ESR, Na +, K+, creatinine, glucose and triglyceride (blood samples were drawn after an overnight fast of at least 8 hours), cholesterol, methylmaleonic acid, albumin, Aspartate aminotransferase (AST), Alanine aminotransferase (ALT), Alkaline phosphatase (ALP), serum calcium, phosphate, vitamin B12, serum iron, serum ferritin, c-reactive protein, thyroid-stimulating hormone, free serum thyroxine, CDT, cortisol, homocysteine, folic acid, anti TPO, cyp 2D6 and cyp 2C9.

Serum samples for inflammation markers are shipped to long-term storage in - 80°C freezer. After all baseline samples are collected, the first series of analyses will be performed with appropriate methods, such as enzyme immunoassays (EIAs). Then the rest will be analyzed after the different time points have been reached.

The patients are included in the BRAIN study and tests for genetic analyses are done according to the BRAIN protocol earlier approved by the Regional Ethics Committee for Middle Norway.

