Health-related quality of life measures have become increasingly important as a type of patient-reported outcome documenting the subjective psychosocial burden associated with chronic illness.

In patients with major depression ECT is widely acknowledged as an effective and appropriate acute treatment. Still questions remain regarding whether ECT is associated with a net improvement in function and quality of life. In recent guidelines from United Kingdom [23] ECT use was restricted until more information becomes available about its effects on memory and quality of life.

A growing body of evidence suggests that inflammation may be linked to depression [24-26]. There are indications that cytokines may cause depressive episodes [27]. Few studies have investigated the immune system in BD. One study found that BD is associated with increased production of the pro-inflammatory cytokines, both in the manic and depressed phase (IL-8 and TNF-α) compared to healthy subjects [28].

Two recent reviews [29,30] concluded that inflammation appears relevant to BD across several important domains and proposed that TNF-alpha modulation is a target for disease-modifying treatment of BD. Further research is warranted to investigate the reciprocal associations between inflammation and symptoms, comorbidities, and treatments in BD.

The aim of the current study is to document the effect size, relative effect size and adverse effects of ECT compared to treatment as usual in treatment resistant bipolar depression. We want to assess the cognitive function in bipolar depression, and how ECT and treatment as usual affect cognitive functioning. Furthermore possible inflammation processes involved in bipolar depression will be investigated. The design enables us to assess changes in a wider spectrum of cytokines as a function of treatment modality and changes in clinical status.

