### Sample size calculation

#### A-priori power calculations

The primary response variable, change in MADRS-score between baseline and endpoint, will be done with the two-sample t-test at the significance level α = 0.05. The least clinical important difference between the treatment group (ECT) and the reference group (drug) to be detected was judged to be 4 in favour of ECT, and a SD = 7 for the change in MADRS is assumed. The possibility of an opposite effect could not be ignored and a two-sided test will be done. Thus the competing hypotheses are:

H0: Mean change in MADRS is the same in both groups vs.

HA: Mean change in MADRS is different in the two groups.

To detect a difference of 4 in mean change in MADRS between the two groups with a power of Π = 0.90 a total of n = 132 patients will have to be included in the analysis. Standard deviations of S= 6-7 are typical for MADRS in studies of patients with BD. The standard deviation for change in score is S√[2(1-R)] where R is the correlation between the two timepoints. Thus, with a correlation of at least 0.5 the standard deviation for the change will be at most S and the power at least 0.90.

Concerning changes in inflammation measures, effects sizes of more than 20-50% are expected, but standard deviations in this population will vary for different cytokines, and a formal power analysis has not been performed.

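### As the assay order reads, average cytokine change from baseline cannot be separated from a shift between assay series, whereas the comparison between arms is largely protected

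*Protocol article*

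**What the plan says.** The Blood samples section sets out how serum for inflammation markers is handled. On storage: "Serum samples for inflammation markers are shipped to long-term storage in - 80°C freezer". On the order of assay: "After all baseline samples are collected, the first series of analyses will be performed with appropriate methods", and "Then the rest will be analyzed after the different time points have been reached". Enzyme immunoassays are named as an example of the method. The section does not mention bridging samples, common calibrators or an adjustment for assay series.

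Table 4 (Assessments) schedules cytokines at visit 1 (before treatment), visit 8 (week 6), visit 9 (week 26) and visit 10 (weeks 30-52), with no distinction by arm.

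The Background section gives the purpose: "The design enables us to assess changes in a wider spectrum of cytokines as a function of treatment modality and changes in clinical status". The section on a-priori power calculations adds that "effects sizes of more than 20-50% are expected" for changes in inflammation measures. It gives no standard deviation and says that no formal power analysis was done for them.

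**The concern.** If the first series holds the baseline samples and later series hold the rest, the split between baseline and follow-up is also the split between assay series. Any systematic difference between series, such as a new kit lot or a different calibration, is added to every patient's change from baseline. It looks like a biological change, and a larger sample does not reduce it.

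The risk is greatest for change from depression to recovery. Table 1 requires a MADRS of 25 or above at inclusion, so the baseline samples come from depressed patients and any remitted or euthymic sample sits in a later series. The section on the primary response variable asks for visit 10 in a euthymic state if possible, which leaves few non-euthymic patients at that visit to compare with.

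At stake is any statement that cytokines rose or fell during treatment within an arm, or between depression and remission in the same patients. The MADRS endpoint is not involved.

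**Working it through.** **Plan's own figures.** The article gives no sample size, standard deviation or assay variability for cytokines, so there is no cytokine figure to reproduce. The total of 132 for MADRS does reproduce. With a difference of 4, SD 7, two-sided alpha 0.05 and power 0.90, the t-test needs 65.3 per arm, rounded up to 66, hence 2 × 66 = 132 with power 0.903. Assay order does not affect it, and it serves below only as the number of patients.

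**Step 1: which contrasts can be identified.** Take one baseline and one follow-up sample per patient, with all follow-up samples in the later series.
- Model with intercept, arm, time and arm × time: 4 columns, rank 4. Adding an indicator for assay series gives 5 columns, still rank 4, because that indicator is identical to time. Mean change from baseline and series shift are therefore not separable from the trial samples alone.
- Model with intercept, clinical state (MADRS change) and assay series: 3 columns, rank 3. Patients within the same series differ in MADRS change, so this association can be estimated.

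**Step 2: size of the bias.** If true change is zero, the apparent change equals the series shift. A shift of 10-20% is an assumption. Against the lower end of the expected effect, 10%/20% = 0.5 and 20%/20% = 1.0. Against the upper end, 10%/50% = 0.2 and 20%/50% = 0.4. These ratios apply only if the expected effect is a within-patient change, which the article does not say.

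**Step 3: consequence for tests.** A simulation used 132 patients, no true cytokine change, and a constant log-scale shift on all follow-up samples. The assumed log-scale SD is about 0.5 and the within-patient correlation 0.5 (a patient component and a visit component, each with SD 0.35). Remitters were represented by patients whose simulated MADRS fell by more than 16 points, a stand-in for the protocol's definition. Proportion of tests with p < 0.05:

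| Series shift | Mean change, all patients | Mean change, remitters only | Difference in change between arms | Correlation with MADRS change |
|---|---|---|---|---|
| 0 | 0.049 | 0.048 | 0.056 | 0.047 |
| 5% | 0.214 | 0.114 | 0.053 | 0.051 |
| 11% | 0.640 | 0.299 | 0.052 | 0.055 |
| 16% | 0.928 | 0.568 | 0.050 | 0.051 |
| 22% | 0.997 | 0.812 | 0.051 | 0.050 |

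A hand check of the first column: SD of change = √(0.35² + 0.35²) = 0.495; standard error = 0.495/√132 = 0.043. A log shift of 0.10 (11%) is 0.10/0.043 = 2.3 standard errors, which gives a rejection rate of about 0.64.

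With a multiplicative shift analysed on the raw scale, the pattern is the same for the same shifts of 5% to 22%: 0.175 to 0.991 for mean change, 0.046 to 0.051 for the difference between arms, and 0.043 to 0.052 for the correlation.

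**Step 4: effect of joint assay.** If all of a patient's samples share a series, the shift drops out of the change. This is the zero row of the table, with 0.049 for mean change.

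**The case against.** The strongest reply is that the Background aim, to "assess changes in a wider spectrum of cytokines as a function of treatment modality and changes in clinical status", is about comparisons between patients, and those survive. A shift common to all follow-up samples cancels when change is compared between arms, compared between remitters and non-remitters, or regressed on MADRS change. This is right. A reader might infer from the assay order that change with treatment and with clinical status is wholly confounded with assay series. The documents do not support that, and the last two columns of the table show why. What remains exposed is uncontrolled change within a group.

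A reader might also infer that no adjustment could ever help because no patient has two visits in one series. That goes too far as well. The article does not say whether the remaining samples form one later series or several. If they form one, contrasts among weeks 6, 26 and 30-52 are free of the problem, and bridging samples would allow an adjustment.

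Two further replies carry some weight. That the first series holds only baseline samples is an inference, though the reference to the rest makes little sense otherwise. And calibrators or bridging controls may be described in a laboratory document not shown, as is usual for a condensed article. The point therefore rests on the order the article states, not on the absence of laboratory detail.

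Finally, cytokines are not listed among the secondary response variables and have no power analysis. That limits the weight of the point but does not remove it.

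**Conclusion.** The concern holds in a limited form. On the natural reading of the Blood samples section, average cytokine change from baseline, within an arm or within remitters, is aligned with assay series. It cannot be separated from a between-series shift without bridging samples or common calibrators. The randomised difference in change, and the association of cytokine change with MADRS change or remission across patients, are largely protected.

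If a shift of 10-20% is assumed, the bias is 50-100% of the lower end of the expected effect, provided that effect means within-patient change. Under the simulation's assumptions, shifts of 11% to 22% would produce a spurious significant mean change in 64% to almost 100% of trials. The shift, the cytokine SD and the within-patient correlation are all assumptions, since the documents give none.

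The primary endpoint and the sample size of 132 are unaffected. This is a worthwhile improvement to an exploratory part of the trial, not a threat to its main result.

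**What to change.** Hold the stored serum until follow-up is complete and assay all of a patient's visits together on the same plate. Put both arms on every plate and include plate as a factor in the model. The serum is already kept at -80°C and the plan already waits for the last baseline sample, so this adds no assays. Its cost is time: the last week-6 sample comes about six weeks after the last patient starts treatment, and the last visit falls by week 52, so baseline-only results come later.

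If an early baseline series is wanted, keep a second baseline aliquot, or set aside bridging samples, and re-assay these with the follow-up samples. That costs one extra aliquot and the repeat assays.

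If the order stays as written without either safeguard, the report should rest on the difference in change between arms and on associations across patients, and should not interpret change from baseline within a group.
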